**Methods:**

In this parallel-group, two-armed, randomized, controlled superiority trial (RCT), 90 participants are assigned to surgical PIP joint denervation or education and exercise. Pain on load 1 year after intervention is the primary outcome measure. Secondary outcome measures include pain at rest, Patient-Rated Wrist and Hand Evaluation (PRWHE), HQ8 score, EQ5D-5L, objective physical function, complications, two-point discrimination, Mini Sollerman, consumption of analgesics, and the need for further surgery. Assessments are performed at baseline, 3 and 6 months, and 1 year after intervention.

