## Background

Osteoarthritis (OA) in the finger joints is very common, especially from middle age and in women, and may cause significant disability. The prevalence of symptomatic hand OA is 26% in women over 70 years of age, with an estimated lifetime risk of OA of 47% among women as compared to 25% in men [1, 2].

Common surgical options for proximal interphalangeal (PIP) joint OA are arthroplasty or arthrodesis. Arthroplasty preserves some motion [3] but has a reported complication rate of 35% 2 years postoperatively [4] and with a complication rate considerably higher than for arthrodesis [3]. A successful fusion is achieved for PIP joint arthrodesis in 95–97% of cases [5, 6] but results in impaired function due to loss of movement. Considering the disadvantages of previously described surgical treatments, there is an unmet need for effective and safe movement-sparing therapies for PIP joint OA.

Surgical joint denervation is a motion-sparing intervention, where sensory articular branches to the joint are sectioned. It has predominately been used in wrist OA, with reported high participant satisfaction, increased grip strength, and improved average pain scores [7]. Case series of PIP joint denervation in 11–54 joints have reported improved pain VAS (0-10) scores of 6–6.4 units [8–10] and an increase in range of motion of 10–25° [8, 9]. A recent systematic review of PIP joint denervation performed through a palmar approach reported 90% participant satisfaction; however, complications were observed in 14%, mainly with transient paresthesia [11]. Hence, there are low-quality evidence of encouraging results after PIP joint denervation, but to our knowledge, there are no randomized controlled studies of PIP joint denervation compared to other types of treatment.

Conservative treatment of finger joint OA includes patient education, exercise, splints, analgesics, or intraarticular glucocorticoid injections. Although patient education and exercise are considered the standard first-line treatments in hip and knee and OA [12], research regarding the effectiveness of these interventions in hand OA is limited. Reports suggest that hand exercise may improve pain and function, joint stiffness, and grip strength [13] and that education and training in ergonomic principles and joint protection also may be effective [14].

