#### Sample size

SPSS version 29 was used for the sample size calculation. The reported MCID of NRS is 20 on a 100-point scale [22]. To our knowledge, the standard deviation (SD) of changes in pain scores in patients with PIP OA have not been previously reported. Hence, the SD is based on an estimation. SD will be calculated at the interim analysis, and the power calculation will be modified if necessary. To show a difference of 20 points in PNRS on load between intervention groups (estimated SD 30) after 12 months, 37 participants are required in each treatment arm. The power will be 80% (*p* < 0.05). To account for non-parametric outcome and loss to follow-up, we aim to include 90 participants in total, 45 in each treatment arm. Participants who withdraw from the trial before intervention will be replaced.

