### Data analyses

The data analyses plan was developed in cooperation with a medical statistician at the Department for Clinical Science and Education, Karolinska Institutet (KI SÖS). Analyses will be performed using an intention-to-treat approach. In addition, per-protocol analysis will be conducted for the primary outcome as sensitivity analysis per the actual treatment received. PROMs will be reported as median (interquartile range (IQR)) and continuous variables as mean (SD). For comparison of the differences between PIP denervation versus patient education and exercise, *T*-test will be used for continuous data with normal distribution, and chi-square tests will be used for categorical data. For non-normally distributed continuous data and ordinal data, the Wilcoxon signed rank tests will be used for within-patient comparisons and rank sum tests for between-patient comparisons. Normality will be assessed by QQ-plots. No subgroup or adjusted analyses are planned. Since there are only two treatment groups, any adjustment for multiple testing is not planned for the primary outcome. Significances of secondary outcomes will be adjusted using the Holm-Bonferroni method to control for multiple significance. Missing data will not be imputed.

The level of significance is set at *p* < 0.05. Demographic data and PROMs from dropouts will be described and compared to the participants that completed the trial. Interim analyses will be performed after 20 and 40 included participants. Data will be analyzed by R or SPSS.

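### The Holm-Bonferroni rule for secondary outcomes also covers complications and sensory measures, so an adjustment meant to limit false claims of benefit makes real harm harder to flag

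*Protocol article*

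**What the plan says.** The rule is in the protocol article, Data analyses: "Significances of secondary outcomes will be adjusted using the Holm-Bonferroni method to control for multiple significance". The same section states "The level of significance is set at *p* < 0.05", plans no adjustment for the primary outcome, and names chi-square tests for categorical data. Nothing there sets safety outcomes apart.

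The abstract (Methods) gives ten secondary entries. The list ends with "complications, two-point discrimination, Mini Sollerman, consumption of analgesics, and the need for further surgery". In the body, Complications to treatment is a subsection under the secondary outcomes heading. It specifies wound infection and loss of sensation, and gives two-point discrimination (S2PD) and Mini Sollerman the task of comparing sensation before and after treatment.

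The Background reports, for the palmar approach, that "complications were observed in 14%, mainly with transient paresthesia". The trial's own procedure uses a volar approach. On size, "we aim to include 90 participants in total, 45 in each treatment arm".

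**The concern.** Family-wise error control limits false positive claims. For efficacy outcomes the false positive is a claim of benefit, and limiting it is sensible. For harms the costlier error is a missed signal, and the adjustment makes that error more likely. The harm threshold also comes to depend on matters unrelated to safety: each extra efficacy measure in the family makes it stricter.

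The Discussion weighs benefit against harm. It presents denervation as attractive partly because earlier reports show few complications, and says it should not be used if it is no better than non-surgical care, because surgery carries risk. Under the stated rules the primary benefit is tested at 0.05, while an excess of complications may have to reach a tenth of that.

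**Working it through.** **The plan's own figure first.** The Sample size section reads "To show a difference of 20 points in PNRS on load between intervention groups (estimated SD 30) after 12 months", and concludes that "37 participants are required in each treatment arm" for 80% power.
- Normal approximation, two-sided 0.05: n = 2 × (1.960 + 0.842)² × 30² / 20² = 35.3, so 36 per arm.
- Noncentral t: power 79.7% at 36 and 80.8% at 37.

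The 37 reproduces. It is sized for pain on load, so it says nothing about power for complications.

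**Inputs for the harm comparison**
- 45 per arm (Sample size).
- 14% complications after denervation (Background).
- 0% on exercise. This is an assumption; the document gives no rate, and zero is the case most favourable to detection.
- m = 10 hypotheses. This is also an assumption: the count of entries in the abstract.
- Chi-square test (Data analyses). Whether it is continuity-corrected is not stated, so both forms are shown.

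**Holm rule.** Order the p-values. The i-th smallest must be at most 0.05/(m − i + 1), and testing stops at the first failure. With m = 10 the first step is 0.05/10 = 0.005.

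**Test of k events against none, n = 45 per arm**
- Uncorrected: X² = 90k/(90 − k)
- Yates: X² = 90(k − 1)²/[k(90 − k)]

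| k v 0 | Uncorrected p | Yates p |
|---|---|---|
| 4 | 0.041 | 0.125 |
| 6 | 0.011 | 0.035 |
| 7 | 0.0059 | 0.018 |
| 8 | 0.0030 | 0.0095 |
| 9 | 0.0016 | 0.0049 |

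Uncorrected, 4 v 0 is enough at 0.05 and 8 v 0 (17.8%) is needed at 0.005. With Yates the counts are 6 and 9. The expected count is 45 × 0.14 = 6.3. A result of 6 v 0 is therefore significant unadjusted under either form, and under neither at 0.005.

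**Chance of significance**, with X binomial(45, 0.14):
- Uncorrected: P(X ≥ 4) = 89% at 0.05; P(X ≥ 8) = 29% at 0.005.
- Yates: P(X ≥ 6) = 62% at 0.05; P(X ≥ 9) = 17% at 0.005. Fisher's exact test gives the same two figures.

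**Full step-down.** The first step is the strictest, so the whole Holm procedure was simulated with 10 hypotheses. Correlation among the other nine was assumed to be 0.4, and each truly affected outcome was given 80% unadjusted power.

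| Other outcomes truly affected | Uncorrected | Yates |
|---|---|---|
| 0 | 29% | 17% |
| 3 | 37% | 17% |
| 5 | 40% | 19% |
| 9 | 58% | 33% |

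**Sensitivity** (uncorrected, first step, m = 10)
- With 2% on exercise, the chance falls from 64% to 15%.
- With 37 evaluable per arm and 0% on exercise, it falls from 78% to 14%.

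**The case against.** **The size depends on choices the document does not make.** The fall from 89% to 29% pairs the test form most favourable to detection with Holm's strictest step. With Yates or Fisher the unadjusted chance is already only 62%, so sparse events cause part of the weakness. Further down the Holm order the loss is smaller. This stands, and is why a range is given. The family size is also assumed. HQ8 has no total score, so the family could exceed 10, but two of its eight items must not be counted again: pain on load is the primary outcome and pain at rest is already listed.

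**The 14% has limits.** It covers all complications and is mainly transient paresthesia. The document gives no rate for lasting sensory loss, nor for change in S2PD or Mini Sollerman. For those measures the point rests on the rule alone.

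**A reader might infer that harm would be concealed, or almost certainly dismissed.** The document does not support that. Suspected complications are recorded at follow-up visits, their frequency is reviewed after 20 and 40 participants, and early termination is considered on frequency, not on an adjusted p-value. No passage makes a safety conclusion depend on significance. The chance of flagging the harm also reaches 58% in one scenario.

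**A reader might also treat further surgery as a harm to be exempted.** The Failure section defines it as treatment failure and follows all patients for it. It could favour denervation, so exempting it would leave a possible benefit claim without error control.

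**Scope.** The exact list of the family may be left to an analysis plan that is not shown. That does not answer the point: the article states the rule for secondary outcomes and lists safety measures among them. The problem is what the rule covers, not that a list is absent.

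**Conclusion.** The point holds. As stated, the Holm-Bonferroni rule includes complications and the sensory measures, and so raises the bar for flagging harm. At the cited 14%, with no events on exercise, 45 per arm and 10 hypotheses, a true excess would be labelled non-significant in about 60% to 71% of trials with the uncorrected test when up to five of the other nine outcomes have real effects. If all nine do, the figure is 42%. With Yates the corresponding figures are about 81% to 83%, and 67%. Without the adjustment they would be 11% (uncorrected) and 38% (Yates).

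The direction does not depend on the assumptions about family size and control rate; the exact percentages do. The consequence is a misleading label in the final comparison, not loss of safety data or of interim review. It is a cheap improvement, best settled before the final analysis.

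**What to change.** Change one sentence in Data analyses, and carry it into the analysis plan:
- Apply Holm-Bonferroni to the secondary efficacy outcomes only. Further surgery, as treatment failure, stays in that family.
- Take complications, loss of sensation, S2PD and Mini Sollerman out of the family. Report them per arm with unadjusted differences and 95% confidence intervals at the visits where they are measured. For S2PD and Mini Sollerman these are 3 and 6 months; neither has a 1-year value.

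As an illustration, 6/45 against 0/45 is a difference of 13.3 percentage points, 95% CI 2.8 to 26.2 (Newcombe), which shows the harm and its uncertainty without a significance label.

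The cost is that harm comparisons carry no family-wise error control, so an occasional false alarm is possible. No extra data or participants are needed. The efficacy family gains slightly: taking three of the ten abstract entries out leaves seven, and the first-step threshold moves from 0.05/10 = 0.005 to 0.05/7 = 0.0071.

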### Randomization, allocation, and blinding

All hand surgeons (> 20) working at the Department of Hand Surgery at Södersjukhuset may enroll participants. The hand surgeon in charge of the participant’s treatment collects informed consent. On the day of enrollment, a dedicated research nurse randomly assigns participants (1:1) to one of the treatment arms using sealed, unnumbered envelopes. A block randomization scheme with a fixed block size of 10 is used. The envelopes containing the allocation slips are prepared and mixed by the primary investigator. Participants are stratified according to sex, since idiopathic OA may be more common in women and men are more likely to have posttraumatic OA than women [18]. Blinding of participants and assessors is considered unfeasible due to a scar on an operated finger. Data analysts are blinded to treatment allocation (anonymized data sheets, with treatment arms coded as A or B by an external part before analyses). Participants in the non-operative treatment group are offered denervation surgery after the study’s primary endpoint (12 months). Cross-over during the study period is not allowed.

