### Retention plan

Participants in both treatment arms are scheduled for regular follow-up visits to promote adherence. Phone numbers and e-mail addresses to the researchers in charge of the trial are provided, should any questions arise. Participants who are unwilling to attend the physical follow-up assessments are offered video meetings instead. Those who do not wish to attend physical or video examinations are asked to fill in the PROMS and send them by mail. Participants that do not show up at scheduled meetings are contacted by telephone and/or mail to be rescheduled for a new appointment. All appointments after enrollment are free of charge. No reimbursements for travel expenses or other costs are provided. In case of dropouts, the reasons for dropping out will be recorded, and the data gathered up to that point will be collected and analyzed.

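### The primary comparison uses only observed 12-month pain, leaves the 3- and 6-month values unused, and has no check for selective loss

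*Protocol article*

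**What the plan says.** The Primary outcome measure section sets pain on load in the included finger, one HQ8 item, at 1 year. The Outcome measures section has patient-reported outcomes collected at baseline, 3, 6 and 12 months, so the same item is available at two earlier follow-up visits.

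The Data analyses section states: "Analyses will be performed using an intention-to-treat approach". Arms are compared by t-test if the data are normal and by rank sum test otherwise. No adjusted analyses are planned, and "Missing data will not be imputed". The one stated sensitivity analysis is per protocol, by treatment received. Dropouts are to be described and compared with completers.

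The Retention plan offers video visits, mailed questionnaires and rescheduling. For dropouts it says "the data gathered up to that point will be collected and analyzed". The randomisation section offers controls denervation after 12 months and adds: "Cross-over during the study period is not allowed".

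**The concern.** A two-sample test at one time point, without imputation, can use only people observed at that time. The protocol does not say so in those words, but it follows from the endpoint, the choice of tests, the absence of adjusted analyses and the no-imputation rule together. It holds whether the 12-month score or its change from baseline is compared.

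Participants know their allocation, so loss could be related to pain and could differ between arms. If controls in pain leave, the remaining control mean is too low and denervation looks less effective than it is. If dissatisfied surgical participants leave, denervation looks more effective than it is. The Discussion says denervation should not be used if it does no better than non-surgical care, so an error in either direction affects the trial's stated conclusion. Describing dropouts beside completers may reveal such a pattern but does not change the estimate.

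**Working it through.** **1. The plan's own figure.** Inputs from the Sample size section: difference 20, SD 30, power 80%, significance level 0.05 (taken as two-sided), 1:1 allocation.

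n per arm = 2 × (1.960 + 0.842)² × (30/20)² = 2 × 7.85 × 2.25 = 35.3, so 36 by the normal approximation. The t-test calculation gives 36.3, so 37, with power 80.8%. The stated 37 reproduces. Raising it to 45 leaves room for 45 − 37 = 8 losses per arm, or 8/45 = 17.8%, if none of the margin is spent on the rank test. This margin protects power. It does not protect against selective loss.

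**2. How selective loss moves the estimate.** Let d be the fraction lost in an arm, and g the amount by which the 12-month pain of those lost would exceed that arm's full mean. The completers' mean is the full mean minus [d/(1 − d)] × g. For the effect, control minus surgical:

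observed = true − [d_c/(1 − d_c)] × g_c + [d_s/(1 − d_s)] × g_s

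With 8 of 45 controls lost, d/(1 − d) = 8/37 = 0.216.
- g = 10 and no surgical loss: 20 − 2.2 = 17.8.
- g = 20 and no surgical loss: 20 − 4.3 = 15.7.
- Random loss (g = 0 in both arms): 20.
- Equal selective loss in both arms: the terms cancel.
- Extreme bound, the eight worst controls lost: shift of −9.5 points.

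**3. Simulation with control-arm loss only.** These assumptions are not in the protocol: normal scores, SD 30 at each visit, true 12-month difference 20, between-visit correlation 0.5 to 0.7, and dropout log-odds rising by 0.5 to 1.5 per SD of pain. The all-visits column predicts missing 12-month values from baseline, 3- and 6-month pain, which approximates a repeated-measures model in large samples.

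| Control loss | Loss depends on | Observed 12-month values only | All visits |
|---|---|---|---|
| 10% | 6-month pain | 17.4–19.3 | 19.9–20.0 |
| 17.8% | 6-month pain | 15.8–18.7 | 19.9–20.1 |
| 30% | 6-month pain | 13.3–17.9 | 20.0–20.1 |
| 10% | unseen 12-month pain | 16.3–18.6 | 17.6–19.4 |
| 17.8% | unseen 12-month pain | 13.9–17.5 | 16.0–18.9 |
| 30% | unseen 12-month pain | 10.2–15.8 | 13.3–18.3 |

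In the second row, t-test power is about 65% to 79%, against 84% with the same loss and no bias.

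**4. Sensitivity to the assumed pattern.** Here there are 45 per arm and visit correlations of 0.4 to 0.65.
- Controls with 6-month pain above 60 drop out at 40%, everyone else at 5% (loss 18% v 5%): 16.8 to 17.0 from observed 12-month values, depending on assumed visit means and simulation error; about 20 using all visits.
- The same 40%/5% rule in both arms, or 20%/5% in controls only: 18.7 to 18.9.
- 20%/5% in both arms: 19.8.
- 15% loss at random: 19.87, so essentially no bias.

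**5. Precision.** In the 40%/5% controls-only scenario the standard error falls from 6.65 to 6.09, a ratio of 0.916. Baseline adjustment alone, at a baseline-to-12-month correlation of 0.4 and with no missing data, gives √(1 − 0.16) = 0.917. Most of the gain therefore comes from adjusting for baseline. Under 15% random loss the ratio is 6.17/6.88 = 0.897.

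**The case against.** The strongest reply is that the protocol limits loss and that the size of the bias comes from assumed inputs. Both points stand. The primary outcome is one questionnaire item that can be mailed in without a visit. Non-attenders are contacted, and the promise of surgery after 12 months gives controls a reason to stay. The protocol states no dropout rate or pattern, and milder or symmetric loss leaves a bias of only about 0.2 to 1.3 points.

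Three stronger readings are tempting but unsupported.
- A reader might infer that the no-imputation rule contradicts intention-to-treat. The protocol sets that term against an analysis by treatment received, so it means analysis as allocated. Leaving out people without outcomes weakens that analysis but does not contradict it.
- A reader might infer a contradiction with the Retention plan. That section does not say dropouts' data enter the 12-month test, and the Data analyses section gives those data a descriptive use.
- A reader might infer that a control in pain can have surgery within the year only by leaving. No passage says so. The Failure section has additional treatment discussed with all patients at 3, 6 and 12 months and records further surgery as an outcome.

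A repeated-measures model is also not a full remedy. Its recovery of 20 points when loss depends on 6-month pain follows from that assumption. When loss depends on unseen 12-month pain, bias remains.

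Finally, generalized estimating equations appear in the abbreviation list, which might suggest a longitudinal analysis was intended. No described analysis uses them.

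**Conclusion.** The point holds as a weakness in the analysis choice, conditional in size. As written, the primary estimate rests on observed 12-month values only, two collected follow-up measurements are unused, and no planned analysis tests the effect of missing values.

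With about 18% selective control loss that depends on 6-month pain, a true 20-point effect would be estimated at about 16 to 19. It would be lower (13.9 to 17.5) if loss depends on unseen pain. The error has the opposite sign if dissatisfied surgical participants are lost, and is near zero if loss is random. These figures rest on the assumed SD, correlations and dropout patterns above. They do not show that bias of this size will occur. The sample size calculation is not in error.

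**What to change.** Make the primary analysis a mixed model for repeated measures of pain on load at 3, 6 and 12 months. Include arm, visit, arm-by-visit, baseline pain with its visit interaction, and sex (the stratification factor), with an unstructured covariance. Include every randomised participant with any follow-up value, as allocated. The 12-month contrast is the primary result, and the rank sum test is kept as a sensitivity analysis. The statement that no adjusted analyses are planned would need to change.

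Add a delta-shift sensitivity analysis: impute missing 12-month values, shift them by fixed amounts separately in each arm, up to at least the protocol's 20-point minimal important difference, and report where the conclusion changes. State in the Retention plan which analyses use dropouts' earlier data.

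Cost: slightly more analysis work, a modelling assumption for an 11-point scale, and a protocol modification, which may need ethics permission under the Trial status section. No new data are needed, and R or SPSS can fit the model. The change should be made before outcomes are examined by arm. Collecting questionnaires after withdrawal would be a change of conduct needing participants' agreement, and is not part of this fix.

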### Withdrawal and safety

In accordance with the ethical permit, participants may withdraw from the trial at any time without giving a reason for doing so and without any negative consequences for their future treatment. PIP denervation has a reported low frequency of complications compared to other surgical options for PIP OA. The most reported complication is transient paresthesia [11]. All surgical procedures induce a low risk of infection. Other than that, the participants are not exposed to any risks. All expected and unexpected complications to treatment are managed at the Department for Hand Surgery at Södersjukhuset. The presence of complications is assessed at the follow-up visits and interim analyses are performed after the inclusion of 20 and 40 participants to assess the frequency of complications. Participants are also provided with contact information to the Department of Hand Surgery and the research team, should any spontaneous adverse event occur. If a high frequency of unexpected complications is noted, the primary investigator will consider early termination of the study. Research participants are covered by Swedish patient insurance (LÖF).

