### Data management and confidentiality

The research team is responsible for trial coordination, conduct, and data management. Data is handled in accordance with the General Data Protection Regulation (GDPR). Data will be transferred from paper-based PROMS to protected electronic databases at Södersjukhuset and Karolinska Institutet. A member of the research group will cross-check the transferred data for errors at interim analyses and before the final analyses. Participants are given an anonymized serial number. The key to the anonymous serial numbers will be kept in protected databases at Södersjukhuset and Karolinska Institutet. Only researchers responsible for the trial have access to the data files and the decoding key. All data will be analyzed anonymized, and results will be presented at a group level. There is no formal data monitoring committee, but the research team will monitor data during interim analyses.

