## Trial status

This is protocol version number 2.0 (from the 14 December 2023). No additional changes have been made hereafter. Any future important protocol modifications require permission from the ethical review board. Recruitment began on 19 September 2023 and recruitment is estimated to be completed in 2027.

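### The interim SD that is to correct the guessed 30 for 12-month pain is triggered by 20 and 40 inclusions, not by completed 12-month outcomes, and will be missing or too imprecise to guide the sample size

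*Protocol article*

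**What the plan says.** The Sample size section targets pain on load at one year: "To show a difference of 20 points in PNRS on load between intervention groups (estimated SD 30) after 12 months", with 37 per arm for 80% power, raised to 45 per arm (90 in total). It acknowledges that no SD of pain change has been reported in this condition and that 30 is an estimate. The remedy it gives is: "SD will be calculated at the interim analysis, and the power calculation will be modified if necessary".

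The timing is in Data analyses: "Interim analyses will be performed after 20 and 40 included participants". Withdrawal and safety uses the same count and names a purpose: "interim analyses are performed after the inclusion of 20 and 40 participants to assess the frequency of complications". Data management and confidentiality adds a check of transferred data at the interim looks and says that there is no formal monitoring committee but that "the research team will monitor data during interim analyses". The Randomization section has the arms coded A or B by an outside party before analyses.

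On pace, Trial status says: "Recruitment began on 19 September 2023 and recruitment is estimated to be completed in 2027".

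**The concern.** The SD re-estimate is the plan's only protection against a wrong guess, and the calculation that it updates concerns the 12-month outcome. A trigger counted in inclusions says nothing about how many people have reached 12 months. With a one-year endpoint and slow accrual, the two counts are far apart.

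The guess matters. If the true SD were 40, 45 per arm would give about 65% power before any dropout (two-sample t-test), and 80% power would need 64 per arm. A re-estimate made too early would have to use 3- or 6-month scores in place of the primary outcome, or else rest on a handful of 12-month scores. The protocol also does not rule out a reduction, so a low estimate arising by chance could shrink the trial.

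**Working it through.** **Reproducing the planned size.** Inputs from Sample size: difference 20, SD 30, power 80%, alpha 0.05 (two-sided, which reproduces the stated figure).

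n per arm = 2 × (SD/difference)² × (1.960 + 0.842)² = 2 × (30/20)² × 7.849 = 35.3, so 36. The exact t-test gives 36.3, so 37, as stated. The planned figure is correct for its inputs.

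**Accrual.** From 19 September 2023 to between 1 January and 31 December 2027 is 39.4 to 51.4 months. Assuming even accrual, the rate is 90/39.4 = 2.28 to 90/51.4 = 1.75 per month.

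**12-month outcomes at each look.** The number with outcomes is (inclusions so far) − (lag × rate), and not below 0. The base case is a 12-month lag from inclusion to outcome.

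| Look | Calendar time | 12-month outcomes |
|---|---|---|
| 20 inclusions | month 8.8 to 11.4 | 0 |
| 40 inclusions | month 17.5 to 22.8 | 40 − 12 × 2.28 = 12.6 to 40 − 12 × 1.75 = 19.0 |

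The endpoint is counted from the intervention, so a wait for surgery lowers these numbers. The protocol does not state a wait. If it were three months (an assumption), the look at 40 would have 40 − 15 × rate = about 6 to 14. If accrual instead rose linearly over the period, the look at 20 would have about 3 to 5 outcomes and the look at 40 about 12 to 17.

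**Precision of the SD.** The 95% interval around an observed SD of 30 is 30 × √(df/χ²), with df = N − 2 and χ² taken at its 97.5% and 2.5% points. The interval limits are then put into the sample-size formula above.

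| N with outcome | 95% interval for the SD | n per arm implied |
|---|---|---|
| 13 | 21.3 to 50.9 | 18 to 102 |
| 19 | 22.5 to 45.0 | 20 to 80 |
| 40 | 24.5 to 38.7 | 24 to 59 |

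For N = 13, for example: 30 × √(11/21.92) = 21.3 and 30 × √(11/3.816) = 50.9. The exact t-test adds about one per arm to each entry.

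**When 40 outcomes exist.** Inclusions by then are 40 + 12 × rate = 61 to 67, or 66 to 74 with a three-month wait (no dropout assumed). Both are below 90, so recruitment is still open.

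**The case against.** Four points can be made for the plan.

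First, the look at 40 is not empty. Some 13 to 19 of 40 participants is a third to nearly half, and the protocol promises a change only if needed, not a mechanical one. This stands: the fault at the second look is imprecision, and it would be wrong to say that almost no 12-month data exist there.

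Second, a reader might infer that the interim looks inflate the 0.05 level, because the protocol waives adjustment for the primary outcome only on the ground that there are two groups. The documents do not support that. The stated uses of the looks are complications, the SD and a data check, and no interim test of efficacy, efficacy stop or futility stop is described. In simulation, re-estimating from the SD alone leaves the type I error at about 5.0% with a blinded pooled SD, and at 5.3 to 5.5% with an unblinded SD and no minimum size. Testing pain at 0.05 with 20, 40 and 90 outcomes would give about 11.5%, but 20 and 40 outcomes will not exist at those looks. One test on 12 to 16 outcomes plus the final test would give about 9.3%, again only if such a test were made.

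Third, a reader might infer that the team sees results by arm. The A/B coding for analysts speaks against this. What remains is that the protocol does not say whether the coding applies at the interim looks. Nor do the several purposes contradict each other, since one look can serve all of them.

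Fourth, whether the SD is pooled and whether the size may only rise are details that a fuller document could hold. That is fair, and they are offered here as parts of the remedy. The mismatch between trigger and endpoint is in the text itself.

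**Conclusion.** The point holds as a mismatch between the trigger and the quantity to be estimated. The first look can supply essentially no 12-month SD. The second supplies one from about 13 to 19 participants, which is compatible with anything from roughly 20 to 80–100 per arm. That is too wide to confirm or correct a plan of 37.

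The result assumes even accrual of 90 participants, completion at some point in 2027 and 12 months from inclusion to outcome. Linearly rising accrual gives a few outcomes at the first look and leaves the second about the same. A wait for surgery lowers the numbers. It also assumes that the interim SD is meant to be that of the 12-month outcome. The protocol does not say so outright, but it follows from the calculation being updated, and an SD of change to 12 months would need the same visits.

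The planned final analysis and its 0.05 level are not affected by anything the protocol describes. The level would be at risk only if pain were compared between arms at an interim look. The point should be fixed but does not threaten the trial's validity.

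**What to change.** - Keep the looks at 20 and 40 inclusions for complications.
- Re-estimate the SD of pain on load once, pooled over arms and without allocation codes, when about 40 participants have the 12-month value. Forty is a reasonable choice rather than the only one.
- Let the sample size only stay at 90 or rise.
- State that the A/B coding in the Randomization section covers the interim looks, and that pain is not compared between arms before the final analysis.

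The cost is a change of wording, which would go through the ethical review board if it counts as an important modification, and a later SD review. Under even accrual with no wait for surgery, the review falls at about month 30 to 35 (40/rate + 12), against month 17.5 to 22.8 for the present second look.
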